# Trial Design:

# Type: Parallel randomized clinical trial

# Allocation ratio: 1:1

# Framework: Superiority

# Aim of the Study:

To assess the ability of antibiotic paste versus calcium hydroxide used as intra-canal medication in reducing pain and level of endotoxins in necrotic teeth with apical periodontitis.

- **PICO approach**

**P:** **population**, patients with non-vital permanent teeth with apical periodontitis.

**I: intervention,** antibiotic paste intra-canal medication.

**C: control,** calcium hydroxide intra-canal medication.

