**O: outcomes:**

|  | **Outcome measure** | **Tool for measurement** | **Unit of measurement** |
| --- | --- | --- | --- |
| Primary | Postoperative Pain | Numerical rating scale (Brunelli et al, 2010) | Ordinal |
| Secondary | Quantification of endotoxins | LAL assay | EU/mL |

Postoperative pain will be measured using Numerical Rating Scale (NRS) after 6, 12, 24 and 48 hours from the end of root canal obturation **(Evaristo et al. 2013)**

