# Research question:

In patients with necrotic teeth and apical periodontitis would the use of antibiotic paste be more effective in reduction of pain and endotoxins than calcium hydroxide or not?

- **Subjects and Methods:**

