**1. Setting and location:**

*** Source of patients**: Out patients of the clinic of endodontic at the faculty of oral and dental medicine, Cairo University, Urban area, Cairo governorate.

*** Operator Qualification:** Post Graduate Master’s Degree Student.

*** Dental units**: Adec 200 U.S.A.

* **X-ray machine**: ViVi, S.r.I, Italy.

* **X-ray film**: Intraoral digital sensor.

1. **Eligibility criteria :**
2. *Inclusion criteria:*
   1. Age between 18-55 years old.
   2. Males or Females.
   3. Maxillary or mandibular single rooted premolar teeth with:

- Non-Vital response of pulp tissue.
- Slight widening in lamina dura.
- Tenderness to percussion.
  1. Positive patients’ acceptance for participation in the study.

1. *Exclusion Criteria*:
   1. Pregnant females: Pain degree change may be due to hormonal change, and some medications are contra indicated.
   2. Patients who had received antibiotic treatment during the last 3 months.
   3. Patients having more than one tooth require root canal treatment.
   4. Teeth with:

- Periodontal probing depth > 4mm.

- Could not be isolated with a rubber dam.

- Fluctuant facial swelling (acute abscess)

- Previous root canal treatment.

- **Final Diagnosis:**
- Mandibular or maxillary single rooted premolar teeth with or without pain.
- Tenderness to percussion.
- On using electric pulp tester it gives response of non-vital pulp.
- On radiographic examination it might have slight widening in lamina dura.
- **Intervention:**

Full medical and dental history using a schematic dental chart will be obtained from all patients treated during this study. Each tooth will be evaluated for vitality (sensitivity) of pulp tissues using electric pulp tester

The patients will be randomly divided into 2 groups:

- ***Experimental group***: antibiotic paste intra-canal medication.
- ***Control group:*** calcium hydroxide intra-canal medication.
- **Sequence of Procedural steps:-**

1. Each patient will be given pain scale chart in order to record his /her pain level before any intervention.
2. Tooth will be anaesthetized using nerve block or infiltration technique by local anesthesia^[[1]](#footnote-1)^.
3. Isolation & disinfection:-

Teeth will be isolated with a rubber dam, and disinfection of their external surfaces will be performed by using 30% hydrogen peroxide followed by 2.5% sodium hypochlorite (NaOCl). Subsequently, 5% sodium thiosulfate will be used to inactivate the disinfectant agents.

1. Access:-

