Root canals will be obturated using lateral condensation technique by proper selection of master cone^[[11]](#footnote-11)^ corresponding to the same size as the master apical file, and then a spreader will be used to allow space for auxillary cones, using resin-based root canal sealer^[[12]](#footnote-12)^

- **Outcomes:**
- **Primary Outcomes:**

The pain scale (0-10 scale) consists of a line anchored by two extremes "No pain" and "the worst pain", patients will be asked to choose the mark that represents their level of pain from 0 to 10, Pain level will be assigned as follow:

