# 0 reading represents “no pain”

# 3 readings represent “mild pain”

# 4- 6 readings represent “moderate pain”

# 7- 10 readings represent “severe pain”

- **Secondary Outcomes:**

The quantitative limulus amoebocyte lysate (LAL) test was used to measure endotoxin concentrations in the root canals by a commercial standard kit. The LAL assay is highly sensitive for detection of minute concentrations of endotoxin. LAL is an aqueous extract of blood cells (amoebocytes) from the horseshoe crab, Limulus polyphemus, that reacts with bacterial endotoxin or LPS. This reaction is the basis of the LAL test, which is used for the detection and quantification of bacterial endotoxins.

- **Participant timeline:**

1. Patients will be selected from the clinic of endodontic after eligibility.
2. They will be randomized and pretreatment diagnosed and radiographed at the same visit of treatment.
3. Patients will be treated in two visits and will record preoperative and postoperative degree of pain at 6, 12, 24 and 48hrs.
4. Patients will return pain charts to the operator on the second visit.

| **periods** | **Recruitment** | **Diagnosis** | **Periapical radiograph** | **Randomization** | **Follow up for postoperative pain** |
| --- | --- | --- | --- | --- | --- |
| Zero |  |  |  |  |  |
| 6 h |  |  |  |  |  |
| 12 h |  |  |  |  |  |
| 24 h |  |  |  |  |  |
| 48 h & close out |  |  |  |  |  |

- **Sample Size:**

The aim of this study is to compare the ability of antibiotic paste versus calcium hydroxide used as intra-canal medication in reducing pain and level of endotoxins in necrotic teeth with apical periodontitis. Based on previous study by Ehrmann, et al. (2003), a medium effect size of approximately 0.25 is expected. A total sample size of 24 patients will be sufficient to detect an effect size of 0.25, a power of 80%, and a significance level of 5%. This number has been increased to a total sample size of 28, to adjust for using nonparametric tests. The number is again increased to a total sample size of 36 (18 in each of the two groups) to allow for losses of around 25%. Sample size was calculated using G*Power program (University of Düsseldorf, Düsseldorf, Germany)^[[13]](#footnote-13)^ . minimal clinical difference 3.5 and 4.5 at 24 hrs and 48 hrs respectively.

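### Teeth with and without pain are both admitted, but preoperative pain enters neither the allocation nor the pain comparison, so chance imbalance and scores of zero can distort or dilute the primary result

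*Protocol*

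**What the plan says.** **Population.** The Final Diagnosis list under Eligibility criteria includes "Mandibular or maxillary single rooted premolar teeth with or without pain". The only pain-related entry sign is "Tenderness to percussion". No minimum score on the numerical rating scale (NRS) is set.

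**Objective.** The aim is to compare the two medications "in reducing pain and level of endotoxins in necrotic teeth with apical periodontitis". The research question asks "would the use of antibiotic paste be more effective in reduction of pain and endotoxins than calcium hydroxide or not".

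**Primary outcome.** "Postoperative pain will be measured using Numerical Rating Scale (NRS) after 6, 12, 24 and 48 hours". The scale has a floor: "patients will be asked to choose the mark that represents their level of pain from 0 to 10".

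**Baseline.** "Each patient will be given pain scale chart in order to record his /her pain level before any intervention". The Randomization section describes one random sequence with no strata. The Statistical analysis section compares pain between the arms by Mann-Whitney at each time. It gives the preoperative score no role in that comparison.

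**Planned size.** The Sample Size section derives 24 patients from an effect size of 0.25, raises this to 28 and then to 36 (18 per arm), and closes with "minimal clinical difference 3.5 and 4.5 at 24 hrs and 48 hrs respectively".

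**The concern.** A patient who scores 0 before treatment cannot show a fall in pain, so the entry rule and the word reduction do not fit together well. Two practical consequences matter more than the wording.

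- **Imbalance.** Preoperative pain plausibly predicts postoperative pain. In a small trial without stratification, one arm can by chance receive more pain-free patients. A test on raw postoperative scores would then credit that arm's paste with the difference.
- **Dilution.** Patients who stay at 0 under either paste add no contrast. They shrink the average difference and reduce power.

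The stated differences of 3.5 and 4.5 points are large on a 0-10 scale. They become harder to reach as the share of zeros rises.

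**Working it through.** **1. The plan's own figure.** Inputs from Sample Size: effect size 0.25, power 80%, alpha 5%. Assumed, because not stated: Cohen's f, a repeated-measures ANOVA with 2 groups and 4 measurements, correlation 0.5, and sphericity. For the within-subject or interaction test, the noncentrality is f² × N × m / (1 − ρ) = 0.0625 × 24 × 4 / 0.5 = 12, on 3 and 66 degrees of freedom. Power is 0.816, so N = 24 is reproduced. Then 24 × 1.15 = 27.6, rounded to 28, and 28 × 1.25 = 35, rounded to an even 36. No step uses 3.5 or 4.5.

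**2. Dilution of a mean difference.** Let D be the required between-arm mean difference. Let p be the share of each arm that is pain-free, and d0 the difference those patients contribute. The remaining patients must differ by (D − p·d0)/(1 − p). The protocol gives neither p nor d0, and does not say whether 3.5 and 4.5 are differences between arms or from baseline. The table takes them as between-arm, with d0 = 0.

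| p | D = 3.5 (24 h) | D = 4.5 (48 h) |
| --- | --- | --- |
| 0 | 3.5 | 4.5 |
| 25% | 3.5/0.75 = 4.7 | 4.5/0.75 = 6.0 |
| 50% | 3.5/0.50 = 7.0 | 4.5/0.50 = 9.0 |

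If pain-free patients contribute 1 point (d0 = 1), the 48 h figure at p = 50% is (4.5 − 0.5)/0.5 = 8.0. With d0 = 0, the requirement passes 10 points above p = 1 − 4.5/10 = 55% at 48 h and above p = 1 − 3.5/10 = 65% at 24 h. Those limits suppose that every other control patient scores 10 and every other experimental patient scores 0.

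**3. Power under a floor.** Simulation of the two-sided Mann-Whitney test at 0.05, one time point, no Bonferroni correction, 1,500 replicates. Each patient has probability p of scoring 0. The others have a control mean of 5 or 6, SD 2 or 3, and a 3.5-point shift before rounding and truncation to 0-10. Means and SDs are assumptions.

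| p | 14 per arm | 18 per arm |
| --- | --- | --- |
| 0 | 0.82-0.99 | 0.90-1.00 |
| 25% | 0.42-0.65 | 0.51-0.79 |
| 50% | 0.16-0.27 | 0.20-0.33 |

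**4. Chance imbalance.** With 18 per arm, the between-arm difference in the pain-free share has a standard deviation of about √(2p(1 − p)/18). This is √(0.375/18) = 0.14 at p = 25% and √(0.5/18) = 0.17 at p = 50%. A gap of 3 patients in 18 (0.17) is therefore ordinary. If pain-free patients stay at 0 and the others average 5, that gap alone moves the mean difference by 0.17 × 5, about 0.8 points, with no effect of either paste.

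**The case against.** The strongest reply is that the primary outcome is postoperative pain, compared between arms at each time, and not change from the patient's own baseline. On that reading, reduction means less pain after treatment with one paste than with the other. A tooth without pain at entry can inform this, because it may become painful after instrumentation. This stands. A reader might infer that admitting pain-free teeth leaves the pain objective unanswerable; the documents do not support that.

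Other parts of the reply also stand:

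- **The sample size does not rest on 3.5 and 4.5.** A reader might take them as the planned differences. They stand as a closing fragment with no link to the effect size of 0.25.
- **The share of zeros is unknown.** Both p and the zero contribution of pain-free patients are assumptions. Every tooth must be tender to percussion. That does not ensure an NRS above 0, but neither does it suggest that scores will stay there.
- **A null result would not be wholly ambiguous.** Preoperative NRS is recorded, so the pain-free share and results by baseline pain can be reported. Even if both medians were 0, a rank test still compares the arms.
- **A minimum entry score is not required.** It would narrow the population and would not guarantee a control mean of 4.5 at 48 h.

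One part does not stand. Baseline adjustment is often left to a statistical analysis plan, but this protocol already names the between-group pain test, and that test ignores the baseline. Stratified allocation cannot be added afterwards.

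**Conclusion.** The concern holds in limited form. The protocol admits a population mixed in preoperative pain, records that pain, and then uses it neither to balance the arms nor to sharpen the stated pain comparison. With 18 per arm, a chance gap of about 14 to 17 percentage points in the pain-free share is one standard deviation if p is 25% to 50%. The imbalance is not systematic over repeated randomisations, but it can distort the one trial that is run.

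The power loss is possible and of unknown size. Under the assumptions shown, it is already substantial when a quarter of each arm stays at 0. The required differences of 4.7 and 6.0 points (p = 25%) or 7.0 and 9.0 points (p = 50%) hold only if 3.5 and 4.5 are between-arm mean differences and those patients contribute nothing. The findings support a change to allocation, analysis and wording. They do not show that the entry rule is wrong.

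**What to change.** - **Randomization:** prepare two allocation lists by preoperative NRS, for example 0-3 versus 4-10, the upper stratum starting at the protocol's moderate band. Use small permuted blocks within each list, since stratifying an unrestricted sequence does not secure balance. The stratum is known in time: the chart is completed before any intervention, and the envelope is opened only after instrumentation.
- **Statistical analysis:** carry the stratum or the baseline NRS into the between-group pain comparison, for instance by a stratified Wilcoxon (van Elteren) test or an ordinal regression with baseline NRS as a covariate. Report the number scoring 0 before treatment in each arm.
- **Aim and research question:** state the pain objective as less postoperative pain in one arm than in the other.
- **Sample Size:** say whether 3.5 and 4.5 are between arms or from baseline. Do not present them as differences the trial is planned to show unless they are justified for a population that includes pain-free teeth.

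The cost is a second envelope set, a possible small inequality in arm sizes from incomplete blocks, and a slightly more complex analysis. No new measurement is needed. Limiting entry to patients with preoperative pain remains open to the sponsor, at the price of slower recruitment and a narrower conclusion.

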# 0 reading represents “no pain”

# 3 readings represent “mild pain”

# 4- 6 readings represent “moderate pain”

# 7- 10 readings represent “severe pain”

- **Secondary Outcomes:**

The quantitative limulus amoebocyte lysate (LAL) test was used to measure endotoxin concentrations in the root canals by a commercial standard kit. The LAL assay is highly sensitive for detection of minute concentrations of endotoxin. LAL is an aqueous extract of blood cells (amoebocytes) from the horseshoe crab, Limulus polyphemus, that reacts with bacterial endotoxin or LPS. This reaction is the basis of the LAL test, which is used for the detection and quantification of bacterial endotoxins.

- **Participant timeline:**

1. Patients will be selected from the clinic of endodontic after eligibility.
2. They will be randomized and pretreatment diagnosed and radiographed at the same visit of treatment.
3. Patients will be treated in two visits and will record preoperative and postoperative degree of pain at 6, 12, 24 and 48hrs.
4. Patients will return pain charts to the operator on the second visit.

| **periods** | **Recruitment** | **Diagnosis** | **Periapical radiograph** | **Randomization** | **Follow up for postoperative pain** |
| --- | --- | --- | --- | --- | --- |
| Zero |  |  |  |  |  |
| 6 h |  |  |  |  |  |
| 12 h |  |  |  |  |  |
| 24 h |  |  |  |  |  |
| 48 h & close out |  |  |  |  |  |

- **Sample Size:**

The aim of this study is to compare the ability of antibiotic paste versus calcium hydroxide used as intra-canal medication in reducing pain and level of endotoxins in necrotic teeth with apical periodontitis. Based on previous study by Ehrmann, et al. (2003), a medium effect size of approximately 0.25 is expected. A total sample size of 24 patients will be sufficient to detect an effect size of 0.25, a power of 80%, and a significance level of 5%. This number has been increased to a total sample size of 28, to adjust for using nonparametric tests. The number is again increased to a total sample size of 36 (18 in each of the two groups) to allow for losses of around 25%. Sample size was calculated using G*Power program (University of Düsseldorf, Düsseldorf, Germany)^[[13]](#footnote-13)^ . minimal clinical difference 3.5 and 4.5 at 24 hrs and 48 hrs respectively.

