A 2-stage access cavity preparation will be performed. The first stage involved the removal of caries without exposure of the pulp chamber by using a high-speed diamond bur. In the second stage, before entering the pulp chamber, the access cavity will be disinfected according to the decontamination protocol described previously. A new bur will be used to access the canal.

1. 1^st^ sample:-

The first endotoxin sample will be taken by introducing the paper points^[[2]](#footnote-2)^ into the full length of the canal (determined by radiographs and apex locator^[[3]](#footnote-3)^) and retaining them in position for 60 seconds. Next, the paper points will be placed in a glass tube and stored at -80^0^C for the LAL assay.

1. Preparation:-

-The root canals will be prepared with Gates-Glidden drills^[[4]](#footnote-4)^ sizes 4, 3 and 2 for the coronal part, and rotary Irace instruments^[[5]](#footnote-5)^ using an endodontic motor^[[6]](#footnote-6)^ with adjusted torque and speed according to the manufacturer's instructions. The rotary files will be introduced inside the canal using EDTA gel^[[7]](#footnote-7)^.

-Before the use of each instrument, irrigation with a syringe (27-G needle) Containing 3ml 2.5% sodium hypochlorite^[[8]](#footnote-8)^.

- Subsequently, 5% sodium thiosulfate will be used to inactivate NaOCl. Then, 5ml saline solution to wash the canal.

1. 2^nd^ sample:-

The second endotoxin sample will be taken as previously described just after the irrigation with saline solution.

1. Intracanal medication:-

The canals will be dried with paper points and filled with intracanal medication plugged into the canal by using Lentulo spiral^[[9]](#footnote-9)^ . The access cavities will be properly filled with Cavit^[[10]](#footnote-10)^.

- **Control group:** Ca (OH)_2_ Paste.
- **Experimental group:** antibiotic paste (ciprofloxacin, metronidazole)

1. The patient will be instructed to record his/her pain level on the pain scale chart after 6 h, 12 h, 24 h and 48 h.
2. 3^rd^ sample:-

After 7 days of intracanal medication, the canal will be accessed under rubber dam isolation by using the protocol for disinfection described previously. The medication will be removed, the final endotoxin sample will be taken just after the irrigation with saline solution.

1. Obturation:-

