**Blinding:**

- The study will be double- blinded which is participants and the assessor.
- Participants will not know which group they will be treated with after they will choose the folded paper inside the opaque envelopes which contain the numbers of each random sequence for both groups.
- Assessor who will assess all results data will not know which group the participants related to (fig.8).
- **Data collection, management, and analysis**
- Baseline Data collection:
- Baseline data will be collected by the operator through a report (Fig.1-5), which comprises of 2 charts (one concerning general health and one concerning the chief complaint related events).
- The report will be anonymous where patients identified by their serial numbers (the first letter of the first and last name and date of birth) only will be registered.
- The full detailed personal data of the patient will be written in a separate sheet having the patient's serial number for further contact with patient, this sheet can be only seen by the operator and the assistant supervisor.
- Outcome data collection: (Fig 6, 7)

Primary outcomes will be collected by the operator through (NRS) which is reliable and valid tool (Brunelli et al, 2010). It is scale consisting of numbers from 0 to 10:

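### The only planned route for the four primary pain scores is a paper chart handed in at the second visit, and the time origin of those scores must be reconciled before any collection rule can work

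*Protocol*

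**What the plan says.** Four places in the Protocol bear on this.

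- **Sequence of Procedural steps.** After the medication is placed: "The patient will be instructed to record his/her pain level on the pain scale chart after 6 h, 12 h, 24 h and 48 h". The next step is the third sample: "After 7 days of intracanal medication, the canal will be accessed under rubber dam isolation". Obturation follows.
- **Participant timeline.** "Patients will be treated in two visits and will record preoperative and postoperative degree of pain at 6, 12, 24 and 48hrs", and then "Patients will return pain charts to the operator on the second visit".
- **Outcomes table (PICO section).** Pain is measured "after 6, 12, 24 and 48 hours from the end of root canal obturation".
- **Sample Size.** The total is raised from 28 to 36 "to allow for losses of around 25" per cent.

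Under Data collection, management, and analysis, the operator collects the primary outcome. A separate sheet of personal data is kept "for further contact with patient, this sheet can be only seen by the operator and the assistant supervisor". The pain chart in the Appendix (Figure 6) has fields for the patient's name and the dentist's telephone number. Nothing links the sheet or the telephone number to collection of the scores.

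**The concern.** All four postoperative readings sit on one sheet of paper held by the patient. On the procedural order, the last reading is due days before the sheet is handed over, and handing it over depends on attending for the next stage of treatment. Someone who withdraws, seeks care elsewhere because of pain, or feels well and stays away would contribute nothing to the primary outcome, even if every reading had been made.

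Attendance may plausibly depend on the pain being measured. The Mann-Whitney comparisons in Statistical analysis would then be made among returners only. The loss allowance in Sample Size replaces numbers; it does not correct selective loss. The wait also gives time to fill in missed entries from memory.

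**Working it through.** **1. The passages side by side**

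| Source in Protocol | Time origin | Are the readings on a chart returned at visit 2? |
|---|---|---|
| Sequence of Procedural steps | Placement of medication (by position in the sequence) | Yes, if made; last due at 48 h, visit 2 after 7 days |
| Outcomes table | End of obturation, which is done at visit 2 | No; they fall after visit 2, and only two visits are planned |

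On the first clock the gap between the last reading and hand-over is 7 days − 2 days = 5 days. On the second clock the return rule cannot deliver the data at all. So the return rule is weak on one clock and unworkable on the other.

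**2. The plan's own numbers**

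Inputs from Sample Size: effect size 0.25, 80% power, 5% significance; totals of 24, 28 and 36.

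- 24: reproduced by a repeated-measures group-by-time interaction test with f = 0.25, 2 groups and 4 measurements (power 0.816). This assumes a correlation of 0.5 and sphericity, neither of which is stated. Whether that test suits the planned pain analysis is a separate matter.
- 28: 24 × 1.15 = 27.6, rounded up. The 15% is assumed.
- 36: 28 × 1.25 = 35, raised to 36 for equal groups. Dividing instead gives 28 / 0.75 = 37.3, or 38 for equal groups.

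**3. How much room the allowance leaves**

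36 − 28 = 8, so at most 8 charts (8/36 = 22.2%) may be lost if 28 are to remain. At exactly 25% loss, 36 × 0.75 = 27 are expected. The binomial probability of at least 28 charts is:

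| Assumed loss rate | 10% | 15% | 20% | 25% | 30% |
|---|---|---|---|---|---|
| P(at least 28 of 36) | 0.99 | 0.92 | 0.72 | 0.44 | 0.20 |

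At the planned rate there is no slack.

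**4. What earlier collection could save**

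Lost charts: 36 × 0.25 = 9. The standard error is proportional to 1/√n, so recovering k of the 9 multiplies it by √(27/(27 + k)).

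| k recovered | 3 | 6 | 9 (ceiling) |
|---|---|---|---|
| Ratio | √(27/30) = 0.949 | √(27/33) = 0.905 | √(27/36) = 0.866 |
| Reduction in SE | 5% | 10% | 13% |

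The documents do not say how many of the losses would occur after the readings were complete, so k is unknown.

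**5. Illustration of bias (assumptions only)**

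Let pA and pB be the proportions lost in each arm, and g the mean difference in NRS score between lost patients and returners, taken as equal in both arms. The returners-only mean difference is then off by (pA − pB) × g.

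Take 6 of 18 lost in one arm and 3 of 18 in the other (9 in all):

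- g = 2: (0.333 − 0.167) × 2 = 0.33
- g = 3: 0.167 × 3 = 0.50
- g = 4: 0.167 × 4 = 0.67

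With equal loss in the arms and the same g, the result is zero. This is on the mean scale; the planned test uses ranks, so it indicates size only.

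**The case against.** **The clock is disputed.** The outcomes table times the readings from obturation. On that definition nothing exists to be lost when visit 2 begins. This stands: the point about losing completed readings holds only on the procedural order, and a reader should not infer that the readings are certainly complete before visit 2. It does not rescue the return rule, which on the other clock asks for a chart before it can be filled in.

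**It argues from silence.** Nothing forbids telephoning a non-attender, and a sheet exists "for further contact with patient". The timeline table labels 48 h as close-out, and the assessor chart (Figure 8) has a date for each reading. This stands in part: ad hoc retrieval is possible, and those entries are ambiguous. Neither establishes a planned earlier collection, and the one stated rule is return at the second visit.

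**Returning a paper diary at the next visit is ordinary.** The patient has a treatment reason to come back, the visit is needed for the third endotoxin sample anyway, and any unsupervised paper chart can be back-filled. That is fair, and it limits the weight of the point. But the Protocol itself plans for sizeable losses, and the remedy needs no extra visit.

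**The size is easily overstated.** A reader might infer that nine charts would be recovered. The 25% covers losses of every kind, including early withdrawals, blank charts and patients who cannot be reached, so nine is a ceiling. A reader might also infer that the comparison will be biased. Nothing in the Protocol shows that attendance differs by arm, and the illustrated 0.33 to 0.67 point is about 7% (0.33/4.5) to 19% (0.67/3.5) of its own minimal clinical differences of 4.5 and 3.5.

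**Conclusion.** The point holds in a limited form. On the procedural order, a missed second visit costs all four primary readings, and the chart can be back-filled for about 5 days. On the outcomes-table clock, the return rule cannot work. Reconciling the outcomes table, the procedural steps and the Participant timeline therefore comes first.

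Earlier collection is a cheap improvement to a weak data-collection rule; it does not correct a numerical error. Its benefit is at most 9 of 36 charts and at most about a 13% smaller standard error, assuming the full 25% loss falls after completed readings and all of it is recovered. Bias is possible but of unknown size, and the figures given for it rest wholly on assumed attendance and pain differences. The Protocol does not support a claim that the trial's result would be invalid.

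**What to change.** 1. **Reconcile the time origin** across the outcomes table, Sequence of Procedural steps and Participant timeline, so that one clock applies to all four readings.
2. **Replace the chart-return sentence in Participant timeline** with: *The four scores are obtained by telephone or text message, by serial number, by the blinded assessor when the 48 h reading is due, counted from the reconciled time origin. The paper chart is kept as a source document and checked when it is returned.* Tying the check to the chart's return, not to visit 2, makes the wording usable on either clock.
3. **State that scores obtained are kept** and analysed in the arm as randomised, even if the patient does not attend later.
4. **Amend Data collection, management, and analysis.** The assessor, not the operator, obtains the scores and receives only the serial number and telephone number. Photographs of the chart showing the patient-name field should not be sent. A side benefit is that the operator, who opens the envelope and places the medication, no longer gathers the primary outcome.

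**Cost:** revised wording, one short contact per patient (36 in all), and limited assessor access to telephone numbers that are now restricted to the operator and assistant supervisor. No extra visit or staff is needed. Patients who cannot be reached will still be lost unless their chart comes back.
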